### Household census

A census of all households in the study area was conducted as a part of phase 1 in order to identify all eligible households for recruitment, obtain informed consent for participation, address eligible households for ease of identification during the data collection phase, and to collect basic information about residents of eligible households. A full household roster was collected and included identifying information, age, date of birth, sex, marital status, literacy, years of education, occupation, tobacco use, weight, height (length for children < 2 yrs), and individual consent status for all household residents. For married women 15–30 yrs and one randomly selected other adult (≥15 yrs), the following additional measurements were collected: FEV_1_, FEV_6_, blood pressure, and heart rate. These people also completed a respiratory symptoms questionnaire.

Assessment of household characteristics was collected for all eligible consented households. Variables collected included measures of household socioeconomic status using an asset index, ethnicity, number and types of cookstoves, house construction materials and size, source of drinking water, household sanitation practices, and whether there were members of the household working outside the local area or country (as a measure of additional cash income).

### Pregnancy identification and data collection

Initial identification of pregnant women occurred at the baseline enrollment visit. Subsequently, all married women between 15 and 30 years of age were visited every 5 weeks and asked about their menstrual period in the preceding 5 weeks. If the woman had her period, the week of the period was recorded and she was visited again 5 weeks later. If she reported no menstrual period, she was offered a urine-based pregnancy test at her home. If the test was positive, she received a pregnancy enrollment interview that included her reproductive history, morbidity in the previous month, date of her last menstrual period, tobacco and alcohol use, and plans for where and by whom she would deliver her baby. We also measured her weight, height, blood pressure, pulse, oxygen saturation, and carboxyhemoglobin level. Pregnant women were encouraged to attend antenatal care clinics in the public or private sector and to deliver at a certified birthing facility. The study provided education on nutrition, clean delivery, and danger signs at this visit. We also provided pregnant women with 90 days of iron-folic acid supplements, a clean birthing kit (included a clean blade, string, plastic tarp, and small plastic disc on which to cut the cord), chlorhexidine ointment for umbilical cord antisepsis, and a single dose of albendazole.

We visited all women monthly throughout their pregnancy to collect pregnancy-related morbidity in the previous month, to ask about tobacco and alcohol use, and to measure weight, blood pressure, pulse, oxygen saturation, and carboxyhemoglobin levels.

### Pregnancy outcome assessment

When a baby was born, the family contacted a local staff member as soon as possible, often during labor. Project staff then visited the home to collect extensive information on the birth process and the health of the mother and newborn infant(s). Birthweight, length, head circumference, and temperature of the infant(s) were measured and recorded. One week following delivery, a visit was made to record information on infant and maternal post-partum morbidity.

### Respiratory morbidity assessment

All eligible children (0 through 35 months of age) were visited weekly for morbidity assessment as described previously. Once a child reached 36 months of age he/she was discharged from the study.

### Cause of death assessment

All women and children who died were identified and a verbal autopsy was conducted with members of the family after a culturally appropriate mourning period.

### Environmental assessment

Each household received a measurement of indoor air quality once prior to new stove installation and once afterwards. This assessment consisted of measurements of PM_2.5_, CO, and temperature and humidity over an 18 hour period that included all the cooking events during the day. All measurements were taken using logging devices set to record every 10 seconds. The instrument used for airborne particulate concentration was the DataRAM pDR 1000AN (Thermo Fisher Scientific Inc., Waltham, MA). This instrument provides particle mass concentration in units of μg/m^3^ and was used in passive mode as a nephelometer. As nephelometric readings vary according to relative humidity, values were corrected based on calibrations with gravimetric measurements as previously described [19]. The instrument for measuring CO concentration data (in units of ppm) was the EL-USB-CO300 (Lascar Electronics Ltd, Salisbury, UK). Temperature and humidity were measured using a HOBO data logger (Onset Computer Corp., Bourne, MA, USA).

### Data management and statistical analysis plans

Interview-based data were collected on paper forms and checked for errors and missing values before being sent from the field site to Kathmandu for data entry. Data entry programs checked for inconsistencies and out of range values. Errors were corrected by data supervisors based on all relevant forms or sent back to the field for clarification if necessary.

### Statistical analysis

The first step in the statistical analysis is calculation of descriptive statistics for exposure, demographic and health outcome data to elucidate basic features in the data, to identify gross outliers and to examine bivariate relationships between pairs of variables. We then proceeded with exposure modeling and health effects analysis at both the individual and village levels for ALRI and birthweight. Throughout, standard software packages such as SAS and R were used, as appropriate.

### Exposure modeling

The raw exposure PM_2.5_ and CO data were pre-processed as follows. First, 10 minute average values were calculated from the 10 second data using 3% trimmed means to avoid undue influence of outliers. The 10 minute averages were then filtered using running medians of length 5 to eliminate short-term excursions caused by larger particle contamination. A base-line value was estimated using the 10th percentile of all measurements for a day. We then defined Stove Influenced Time (SIT) to be any 10-minute interval for which it’s filtered value exceeded the baseline by a multiple of more than 1.2. We defined the Stove Influenced Particulate (SIP) or CO (SIC) as the total difference between the 10-minute average value and the baseline, over the SIT times for a 24 hour period.

For each exposure measure, we used a linear mixed effects regression model as defined below to estimate the average difference between households with an improved stove as compared to control households without one, while controlling for season and secular trend. Because the effect of the stove on indoor air quality can vary by season, we considered two measures: (1) the average household exposure for the year after stove installation as compared to the annual average before; and (2) the average change in exposure immediately after stove installation was done as compared to immediately before. The former captures the season-specific effects of stoves but can be biased by secular trends. The latter is less biased, but more variable and more dependent on the adjustment for seasonal and secular trends.

### Health effects modeling

To estimate the effect on ALRI of having a new cook stove installed in the home, while fully accounting for the salient features of the stepped wedge trial design [20] and for sources of variation at both the individual and village levels, we used a generalized mixed effects model as summarized in Hussey and Hughes [20]. Let *Y*_*ijt*_ denote a positive ALRI response for individual *j* = 1,…,*N* from village *i* = 1,…,*I* at time point *t* = 1,…,*T*. Let *p*_*ijt*_ denote the risk of ALRI, that is the expected value for *Y*_*ijt*_. We assume *p*_*ijt*_ satisfies the logistic random effects model:
1

where: *α*_0_ is the overall baseline log odds of having ALRI;  is the random effect for cluster *i* to account for correlation among children from the same village*;* is the random effect for child j in cluster *i* to account for possible within-child-level correlation; *s*(*t*, *v*) is a fixed, smooth function of time to control for secular and seasonal trends; and *θ* is the fixed cook stove intervention effect that is of primary scientific interest. In this model, we will represent *s*(*t*, *v*) by natural cubic splines with *v* degrees of freedom. A priori, with two years of data, we chose *v* = 8 (4 degrees of freedom per year) but will conduct sensitivity analyses to determine whether the major findings are sensitive to this choice over a range of reasonable choices *v* = 4 to 12 for this smoothness constraint. The generalized linear mixed model above will be estimated using the method of maximum likelihood as implemented in the R package *glmer (*http://cran.r-project.org/web/packages/lme4/lme4.pdf*)*. Robust variance estimates of the stove effect coefficient will be calculated and compared to the model based values as a sensitivity analysis to check on the assumed correlation model within children and among children within villages. If the robust variances are significantly larger than their model-based counterparts, the former will be used for testing and confidence interval calculations.

A similar approach will be used to estimate the treatment effect on birthweight. While seasonality of birthweight and other reproductive outcomes is present in this population, it is not as dramatic as seen for ALRI, nor is the clustering by sector as high [16]. Birthweight will be treated as both a continuous variable and as dichotomous with low birthweight defined as weights <2500 g.

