The degrees of freedom *v* used in specifying the time function *s*(*t*; *v*) was allowed to vary between 0 (no secular trend) to 8 (4 per year). When the data are generated without a secular trend, all three values for *v* produce consistent estimates of the cook stove effect. However, when in the case where there is a sizeable trend, the *v* = 2,8 models give consistent estimates, but the model that ignores the trend produces strongly biases estimates. The simulation study shows that the design has adequate poser to detect a decrease of 20% or greater relative to baseline (Table 2).

**Table 2 Tab2:** **Power to compare ALRI incidence before and after alternative biomass cookstove installed for varying relative odds and degrees of trend in ALRI rates over time**

	True cook-stove effect (θ)								
	(Relative odds)								
Degree of trend in ALRI incidence	−0.1			−0.2			−0.3		
ν	0	2	8	0	2	8	0	2	8
No trend	88	26	34	100	81	89	100	99	99
Large trend	100	19	37	100	80	87	100	99	99

Based on previous research in this study area, we originally expected approximately 6000 live births in the study area for these trials over 4 years. However fertility declined significantly since that previous research was conducted and a modified expectation was in the range of 3000 live births. Approximately 1% died prior to our being able to weigh them leaving approximately 2350 live births in phase one and 600 in phase two. The mean birthweight in our last trial was 2700 grams with a standard deviation of 437 grams [21]. The intra-sector correlation for birthweight was estimated to be 0.03357. Assuming 80% power and a Type I error of 5% (2- sided), the minimum detectable mean difference in birthweight was approximately 57 g in phase 1 and 83 g in phase two. These detectable differences in mean birthweight are in the range of those reported for infants whose non-smoking mothers are exposed to second hand tobacco smoke during pregnancy and well below the mean differences between women who do and do not smoke during pregnancy.

The rate of low birthweight (<2500 grams) was 29% in our most recent trial in this area and the cluster related design effect for the proportion born low birthweight was 2.36. Assuming a Type I error of 5% (2-sided), a 20% treatment effect, and sample size of 1175 enrolled live births before stove installation and an equivalent number after installation, the power was >80% for phase one but only 47% for phase two.

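### As described, the continuous birthweight analysis leaves out prognostic variables the trial already collects, at a modest cost in precision and with no bias

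*Protocol article*

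**What the plan says.** The Health effects modeling section defines the terms of the ALRI model one by one: an intercept, a village random effect, a child random effect, a smooth function of time with 8 degrees of freedom, and the stove effect. The equation itself is not legible in the text at hand, but these definitions accompany it. The section also fixes a sensitivity range for the spline, the software, and a rule for switching to robust variances. For birthweight it adds: "A similar approach will be used to estimate the treatment effect on birthweight". Birthweight is to be analysed both as a continuous variable and as below or above 2500 g. No section mentions covariate adjustment, and phase two has no separate health model.

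Candidate covariates are collected:

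- At pregnancy enrollment (Pregnancy identification and data collection): "she received a pregnancy enrollment interview that included her reproductive history", and "We also measured her weight, height, blood pressure, pulse, oxygen saturation, and carboxyhemoglobin level".
- In the roster (Household census): "age, date of birth, sex, marital status, literacy, years of education".
- In the same section, household ethnicity and an asset index of socioeconomic status.

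The Pregnancy outcome assessment section allows for more than one infant at a birth. It names weight, length, head circumference and temperature, but no field for newborn sex or for singleton or multiple birth.

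**The concern.** Birthweight is a primary outcome, and the Sample size section reports that expected live births dropped from about 6000 to about 3000. With fewer births, residual variance bears more heavily on what the trials can detect. In a linear model for birthweight, adjusting for baseline variables that predict the outcome lowers the residual variance and so the standard error of the stove effect. A model with only time and stove as fixed effects gives up that gain although the data are in hand. What is at stake is precision, not validity: leaving the covariates out does not bias the randomised comparison.

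**Working it through.** **Inputs** (Sample size section unless noted)

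- "The mean birthweight in our last trial was 2700 grams with a standard deviation of 437 grams"
- "The intra-sector correlation for birthweight was estimated to be 0.03357"
- Births with a weight: "leaving approximately 2350 live births in phase one and 600 in phase two". Phase one splits as 1175 before and 1175 after installation. For phase two I assume 1:1 allocation, so 300 per arm.
- 80% power and two-sided 5%, giving a multiplier of 1.960 + 0.842 = 2.802.
- 51 sectors (Design section).
- R², the share of birthweight variance explained by the covariates: not given. I assume 0.05 to 0.15.

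**The plan's own figures.** The article states detectable differences of 57 g (phase one) and 83 g (phase two). With MDD = 2.802 × SD × √(2/n per arm):

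- Phase two: SE = 437 × √(2/300) = 35.7 g, and MDD = 2.802 × 35.7 = 100 g, not 83 g. Reaching 83 g would need about 435 per arm.
- Phase one with no clustering: 2.802 × 437 × √(2/1175) = 50.5 g, not 57 g.
- Phase one under the model described: generalised least squares with a sector random effect at the stated correlation, 24 months, 12 crossover groups, births spread evenly, and a time spline with 8 degrees of freedom. This gives about 94 g (93.8 g with 51 sectors, 94.0 g with the 48 of the power simulation).

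That the stated figures do not reproduce is a separate matter. The proportional gain below does not depend on it.

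**Effect of covariates.** The residual SD, and with it the SE and MDD, is multiplied by √(1 − R²). The equivalent increase in births is 1/(1 − R²) − 1.

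| Assumed R² | SE factor | Phase two MDD | Phase one MDD (time-adjusted) | Equivalent extra births |
|---|---|---|---|---|
| 0 | 1 | 100 g | 94 g | – |
| 0.05 | 0.975 | 97 g | 92 g | 5% |
| 0.10 | 0.949 | 95 g | 89 g | 11% |
| 0.15 | 0.922 | 92 g | 87 g | 18% |

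Starting instead from the stated figures, 57 g becomes 55.6 to 52.6 g and 83 g becomes 80.9 to 76.5 g.

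**In terms of power.** The Background cites a 97 g lower birthweight with biomass smoke exposure. This is an observational association, not the design difference for phase two, and serves only as a yardstick. Power = Φ(97/SE − 1.960). With SE = 35.7 g it is 78%. At R² = 0.05 (SE 34.8 g) it is 80%, and at R² = 0.15 (SE 32.9 g) it is 84%.

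**The case against.** The best counter-argument is that this reasons from silence. The birthweight model is one sentence, and it cannot copy the ALRI model term for term: the outcome is continuous, and one weight per infant leaves nothing for a child random effect to do. A condensed article commonly leaves a covariate list to the analysis plan, which is not shown. So the text does not prove that the final analysis will be unadjusted. That stands, and it is why the point is limited to the analysis as described. It does not remove the point, because the section goes into detail on spline, software and variance rule, and the approach it carries over to birthweight has no prognostic term. An unadjusted primary analysis is valid; it is only less efficient.

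A reader might infer more than the documents support:

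- *That the covariates are strong predictors.* No R² or correlation is given. At 5% the gain is small.
- *That the ALRI model needs age adjustment for the same reason.* A rough calculation, itself resting on an assumed age effect, puts the gain at no more than about 2.4% of the standard error. The model is logistic, so adding age also changes the conditional odds ratio being estimated rather than simply narrowing its interval. The same caution applies to low birthweight as a yes/no outcome.
- *That chance imbalance is likely with 12 randomised groups.* In phase one, sectors contribute time before and after installation and are spread geographically within groups. Phase two is randomised by household within VDC and ward.
- *That the plan admits low power for mean birthweight in phase two.* The 47% it reports is for the low birthweight proportion with a 20% effect. For the mean, it claims 80% power at 83 g.
- *That adjustment is the only way to gain precision.* Nothing in the documents shows this.

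**Conclusion.** The point holds for continuous birthweight in both phases, as a missed gain in efficiency and not an error that threatens validity. Its size rests on an R² the documents do not supply. Over the assumed 5 to 15% the benefit is modest, equal to roughly 5 to 18% more births. The phase two figures also assume 300 births per arm and no clustering; the phase one figures assume births spread evenly over sectors and months. The case for acting is that the gain is nearly free.

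**What to change.** State in the primary analysis of continuous birthweight, for both phases, a short fixed list: maternal height, maternal age, parity from the reproductive history, and ethnicity or the asset index. Add infant sex and singleton or multiple birth if the birth record holds them; the article does not show that it does.

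Leave out gestational age, which is itself a primary outcome. Leave out maternal weight, blood pressure and carboxyhemoglobin measured in pregnancy, since these can follow installation and could lie on the path from stove to birthweight. Report the unadjusted model as a sensitivity analysis.

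Fix the list before stove effects are estimated, because the Statistical analysis section begins by looking at bivariate relationships and covariates should not be chosen from those.

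The cost is a few lines of analysis text and a simple, stated rule for the few missing covariate values. The core list needs no new data.

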### Sample size

The power of the study to test the null hypothesis that the stove installment effect is zero (*θ* = 0) for the ALRI outcomes was done as follows. We adopted the design represented in Figure 1 with 12 groups of sectors and explain the sample size calculation using the notation from the statistical plan in the previous section. We set the true value the stove effect to take values between *θ* = −0.1 to −0.3 corresponding to 10 to 30% reductions in the odds of ALRI attributable to installation of the clean cook stove. To estimate the power, we specify the parameters of the design and study population as via the following assumptions:The number of eligible children per sector follows a Poisson distribution with mean 35.The ALRI rate will be approximately 1.0 episodes per child per year, conservatively lower than the value 1.3 observed in previous studies in the same area [15].There will be 4 sectors in each of the 12 groups.Seasonality is represented by a sinusoid with relative amplitude of 1.05 so that the peaks and troughs have ALRI rates that are 1.05 times higher or lower than the long-term average.There are two cases for secular trend: (5a) no secular trend; (5b) a large trend that starts at time 1 with a 50% increase in the odds of ALRI and decreases to 0 over 10 months.The random effects variances for village and child are 0.025 and 0.10 respectively. These values imply that villages can have ALRI rates that vary by ±30% (2*√.025) across the population while individuals within a village have rates that vary by ±60% (2*√.1).

To estimate power, we conducted a simulation study in which we first generated a random data set given the parameters described above, then estimated cook-stove affect parameter using the generalized linear mixed effects model specified in Equation (1) above. The simulation was run 100 times for each situation and the estimated power is reported in the table below with standard error of the power less than 5%.

The degrees of freedom *v* used in specifying the time function *s*(*t*; *v*) was allowed to vary between 0 (no secular trend) to 8 (4 per year). When the data are generated without a secular trend, all three values for *v* produce consistent estimates of the cook stove effect. However, when in the case where there is a sizeable trend, the *v* = 2,8 models give consistent estimates, but the model that ignores the trend produces strongly biases estimates. The simulation study shows that the design has adequate poser to detect a decrease of 20% or greater relative to baseline (Table 2).

**Table 2 Tab2:** **Power to compare ALRI incidence before and after alternative biomass cookstove installed for varying relative odds and degrees of trend in ALRI rates over time**

	True cook-stove effect (θ)								
	(Relative odds)								
Degree of trend in ALRI incidence	−0.1			−0.2			−0.3		
ν	0	2	8	0	2	8	0	2	8
No trend	88	26	34	100	81	89	100	99	99
Large trend	100	19	37	100	80	87	100	99	99

Based on previous research in this study area, we originally expected approximately 6000 live births in the study area for these trials over 4 years. However fertility declined significantly since that previous research was conducted and a modified expectation was in the range of 3000 live births. Approximately 1% died prior to our being able to weigh them leaving approximately 2350 live births in phase one and 600 in phase two. The mean birthweight in our last trial was 2700 grams with a standard deviation of 437 grams [21]. The intra-sector correlation for birthweight was estimated to be 0.03357. Assuming 80% power and a Type I error of 5% (2- sided), the minimum detectable mean difference in birthweight was approximately 57 g in phase 1 and 83 g in phase two. These detectable differences in mean birthweight are in the range of those reported for infants whose non-smoking mothers are exposed to second hand tobacco smoke during pregnancy and well below the mean differences between women who do and do not smoke during pregnancy.

The rate of low birthweight (<2500 grams) was 29% in our most recent trial in this area and the cluster related design effect for the proportion born low birthweight was 2.36. Assuming a Type I error of 5% (2-sided), a 20% treatment effect, and sample size of 1175 enrolled live births before stove installation and an equivalent number after installation, the power was >80% for phase one but only 47% for phase two.

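### The phase-one detectable birthweight difference of 57 g follows neither from the stated 2350 births nor from the planned time-adjusted analysis, which needs about 93–101 g

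*Protocol article*

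**What the plan says.** The Sample size section of the protocol article gives these birthweight inputs: "The mean birthweight in our last trial was 2700 grams with a standard deviation of 437 grams"; "The intra-sector correlation for birthweight was estimated to be 0.03357"; and, after early deaths, "leaving approximately 2350 live births in phase one and 600 in phase two". From these, at 80% power and a two-sided 5% level, it concludes that "the minimum detectable mean difference in birthweight was approximately 57 g in phase 1 and 83 g in phase two". The next paragraph, on low birthweight, divides phase one as a "sample size of 1175 enrolled live births before stove installation and an equivalent number after installation", so 2350 is the total and each side of the comparison has 1175. It claims more than 80% power for phase one and 47% for phase two.

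On the analysis, Health effects modeling describes the ALRI model as a mixed model with a cluster random effect and a natural cubic spline of calendar time (8 degrees of freedom a priori, 4 to 12 in sensitivity analyses) for secular and seasonal trend. It then says: "A similar approach will be used to estimate the treatment effect on birthweight". It adds that birthweight is less seasonal than ALRI, but does not withdraw the time term.

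**The concern.** Two things do not fit. First, 57 g cannot be obtained from 1175 births before and 1175 after by any usual formula with the stated SD and intra-sector correlation. Second, in a stepped wedge the share of households with a new stove rises with calendar time, so adjusting for time removes much of the stove contrast. For ALRI the article simulates power with that adjustment, and warns that where there is a sizeable trend "the model that ignores the trend produces strongly biases estimates". The birthweight paragraph beside it makes no such allowance.

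Birthweight is a primary outcome. The article uses the two detectable differences to place the trials within the range of passive-smoke effects. If 57 g is read as what phase one could detect, a null result will be taken as stronger evidence of no effect than the design can supply.

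**Working it through.** **Inputs.** From Sample size: SD 437 g, ICC 0.03357, 2350 births in phase one and 600 in phase two, 80% power, two-sided 5%. From Design: 51 sectors, 12 randomized groups, 6 + 12 + 6 = 24 months. The ALRI power assumptions use 4 × 12 = 48 sectors, so both counts are shown. z = 1.960 + 0.842 = 2.802.

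**Step 1: reproduce the stated figures.** The formula is MDD = z × SD × √(2 × DE / n), with DE = 1 + (m − 1) × 0.03357, m births per sector and n births per group.

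| Phase | n per group | m (51 / 48 sectors) | DE | MDD | Stated |
|---|---|---|---|---|---|
| One | 2350 | 46.1 / 49.0 | 2.51 / 2.61 | 56.6 / 57.7 g | 57 g |
| Two | 600 | 11.8 / 12.5 | 1.36 / 1.39 | 82.5 / 83.2 g | 83 g |

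Both figures appear, but only with the phase total used as the size of each group.

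**Step 2: use the article's own group sizes.**
- Phase one, n = 1175, no clustering: 2.802 × 437 × √(2/1175) = 50.5 g.
- Phase one, n = 1175, DE at 23.0–24.5 births per sector and period (1.74–1.79): 66.6–67.5 g.
- Phase one, n = 1175, DE 2.51–2.61 as in Step 1: 80.1–81.6 g.
- Phase two, n = 300, no clustering: 2.802 × 437 × √(2/300) = 100 g.

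None of these is 57 g or 83 g.

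**Step 3: low birthweight.** A 20% effect takes 29% to 0.8 × 29% = 23.2%. With the stated design effect of 2.36, 1175 per group is 1175/2.36 = 498 effective births, and power is about 55%. Entering 2350 per group gives 996 effective births and 84%, which matches the claim of more than 80%. This is the same pattern as in Step 1.

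**Step 4: the planned model.** I took the generalized least squares variance of a linear mixed model with a sector random intercept, a stove term and fixed time terms. It uses 12 sequences, 24 months and 2350 births spread evenly.

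| Time terms | MDD, whole-month exposure | MDD, installation month half exposed |
|---|---|---|
| None | 51 g | 52 g |
| Season only (harmonic or calendar month) | 53–54 g | 54–55 g |
| Spline, v = 4 to 12, or monthly effects | 93–94 g | 100–101 g |

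With the spline, the standard error at 51 sectors is 93.1/2.802 = 33.2 g. Power at a true 57 g is then Φ(57/33.2 − 1.96), about 40%, or about 36% with half-month coding (standard error 35.7 g). Without time terms it is 88%.

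The spline result is stable: 87–94 g for an ICC from 0.001 to 0.10, 88–93 g if the within-sector correlation weakens over time, and 97 g if the effect begins nine months after installation.

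**Step 5: compare with the article's Table 2.** For ALRI at θ = −0.1 without trend, power falls from 88% (v = 0) to 34% (v = 8). The implied ratio of standard errors is (1.175 + 1.960)/(−0.412 + 1.960) = 2.0. For birthweight the ratio is 93.1/51.1 = 1.8, so the loss is of the same order.

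**The case against.** The strongest reply is that the time-adjusted figure rests on an inference. The article says only that the approach for birthweight will be similar. It fixes no spline for that outcome, calls birthweight less seasonal, and adds six-month periods at each end to balance season. If only season were adjusted for, the detectable difference would be 53–55 g and 57 g would be slightly conservative. That stands as a condition on the 93–101 g. It does not rescue the text: the spline being carried over is defined for secular as well as seasonal trend, nothing says the secular part is dropped, and 57 g does not follow from the stated group sizes anyway.

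A second reply is that births were fixed by falling fertility, which the article discloses, so the figure drove no recruitment decision and the eventual confidence interval will show the precision reached. That is fair, and it limits the harm to how results are read beforehand.

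Three stronger readings are tempting, and the documents do not support them.
- A reader might infer that 57 g is an unadjusted before/after comparison, or that clustering was nearly ignored. The unadjusted comparison gives 50.5 g, and the reconstruction that fits uses the full ICC at 46–49 births per sector.
- A reader might infer that the passive-smoke claim is false. The article gives no numeric range for those effects, so nothing shows that 93 g lies outside it.
- A reader might infer that phase one would miss any realistic effect. No realistic effect is defined, and the 97 g in the Background is an observational estimate from literature the article itself calls variable in quality, not a design target.

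**Conclusion.** The point holds. The stated 57 g has two separate faults: a sample size per group that appears to be doubled, and no allowance for time adjustment. Correcting the first alone gives about 80–82 g under the same parallel-group formula. That formula does not describe a wedge either, because each sector contributes births both before and after installation. The figure that matches the planned model is about 93–94 g, or 100–101 g with the installation month half exposed, so the stated value is roughly 40% too small (57/93 = 0.61; 57/101 = 0.56).

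The doubling is a reconstruction, since no formula is printed, but it fits 57 g, 83 g and the phase-one low-birthweight power together. The model-based figure assumes births even over sectors and months, an immediate and constant effect, exposure defined by stove status at birth, and a time term that covers secular trend. The article does not define exposure for a pregnancy that spans installation.

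**What to change.** - Restate the phase-one detectable difference from the model that will be fitted, with 2350 as the total. On the assumptions above it is about 93–101 g. State the time terms and the exposure definition for birthweight alongside it.
- Recompute phase two with 300 per arm. Without clustering it is 100 g, not 83 g.
- Recheck the low-birthweight power. At 1175 per group with design effect 2.36 it is about 55% before any time adjustment. The phase-two 47% needs the same check, since 300 per arm without clustering gives about 37%.
- Re-examine the sentence that compares the detectable differences with passive-smoke effects against the corrected figures, giving the range it relies on.

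The cost is one recalculation and a few sentences. The downside is less favourable stated figures.
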